## Abstract

**Background:**

Veterans with serious mental illness (SMI) have significantly elevated suicide risk compared to those without SMI. This group may also experience cognitive and functional impairments that complicate suicide prevention care.

**Objective:**

We detail a pilot randomized controlled trial protocol evaluating a novel peer specialist–delivered suicide prevention intervention tailored to SMI called Suicide Prevention by Peers Offering Recovery Tactics (SUPPORT). In SUPPORT, peer specialists are trained in foundational suicide prevention information and intervention delivery. Once a week for 50 minutes, a peer specialist meets with a veteran via telehealth or in person to deliver the 4 SUPPORT modules that focus on recovery and suicide prevention. The peer specialist conducts 2 check-in calls at 2 and 4 weeks after the final module to reinforce the intervention material and offer additional resources. Aim 1 will evaluate the feasibility and acceptability of SUPPORT. Aim 2 will determine the preliminary impact of SUPPORT versus enhanced standard care on personal recovery and suicide ideation severity (primary outcomes), as well as domains of veteran functioning (secondary outcomes). Standard care is enhanced such that all veterans receive additional suicide risk assessment, which may result in additional clinical interaction.

**Methods:**

A pilot randomized controlled trial with 50 veterans randomized into 2 groups will be conducted. Participants will be recruited from the Veterans Affairs San Diego Healthcare System. Veterans with SMI and past-1-month active suicide thoughts or past-3-month suicide behavior as defined by the Columbia–Suicide Severity Rating Scale will be included. Enrolled veterans will be randomized to receive SUPPORT or enhanced standard care. All veteran participants will be assessed at baseline and the 1-, 2-, and 3-month follow-up assessments. Feasibility is defined as attainment of recruitment goals and a ≥70% retention rate. Acceptability for veterans is measured using the Client Satisfaction Questionnaire–8. Acceptability for peer specialists is measured using a satisfaction question rated on a 5-point Likert scale. Primary outcomes are measured using the Recovery Assessment Scale–41 (personal recovery), as well as the Beck Scale for Suicide Ideation and the Columbia–Suicide Severity Rating Scale (suicide ideation severity). Secondary outcomes are measured using the Specific Level of Functioning Scale (functioning), the brief version of the World Health Organization Quality of Life Scale (quality of life), and a laboratory-developed self-knowledge task (suicide prevention strategy recall). Outcomes will be tested using mixed-effects models. Safety procedures for all participants are discussed.

**Results:**

This trial was funded in November 2022. Community-engaged intervention and protocol refinement were completed in January 2025. Data collection for the randomized controlled trial began in January 2025.

**Conclusions:**

By combining training for peer specialists with a novel recovery-oriented suicide prevention intervention, SUPPORT helps establish a role for peer specialists in suicide prevention and addressing suicide in veterans with SMI.

**Trial Registration:**

ClinicalTrials.gov NCT05537376; https://clinicaltrials.gov/study/NCT05537376

**International Registered Report Identifier (IRRID):**

DERR1-10.2196/66182

## Introduction

### Background

Among the veteran population, those with a serious mental illness (SMI), particularly veterans with bipolar disorder or schizophrenia spectrum disorders, are at markedly elevated suicide risk compared to veterans without SMI and nonveterans with SMI [1]. Making suicide prevention care challenging, people with SMI are often excluded from suicide-related treatment options [2,3]. There are also different means of suicide used, such as self-stabbing [4], as well as functional and cognitive impairments that may alter uptake of suicide prevention strategies in this group [5,6]. To address these unmet needs, we provide the rationale, design, and clinical pilot randomized controlled trial protocol for a novel augmentative peer-delivered, recovery-oriented suicide prevention intervention for veterans with SMI.

Several psychosocial rehabilitation initiatives in the Veterans Health Administration (VHA) have included individuals with lived experience (“peers,” now known as “peer specialists”) to support veterans with a wide range of mental health experiences [7]. In the context of VHA mental health care, peer specialists are defined as veterans with lived experience in recovery [8] from mental illness who are specifically trained, certified, and employed [9] to share their recovery story to support other veterans also experiencing mental illness [10,11]. Numbering approximately 1400 in VHA in 2024, peer specialists play an adjunctive yet integral role in VHA health care [7,12]. However, there is a dearth of existing interventions that use peer support services in suicide prevention initiatives [13-15] Reviews of this literature have concluded that the use of peer specialists for suicide prevention is feasible [13,14]. VHA peer specialist administrative data show that 8% are already working directly with veterans at high risk of suicide [16]. Moreover, peer support has been shown to be a positive adjunct to VHA suicide prevention initiatives by filling an existing gap [17]. Although there is limited suicide prevention training for peer specialists, VHA peer specialists report interest in receiving such specific training [11,18]. Thus, there is a tremendous opportunity to involve peer specialists in VHA suicide prevention initiatives.

### Objectives

The Suicide Prevention by Peers Offering Recovery Tactics (SUPPORT) program was co-developed by peer specialists and veterans with SMI along with scientific experts in the field [18]. The SUPPORT program includes training tailored to a peer’s scope of practice in suicide prevention (SUPPORT 101) and a recovery-oriented suicide prevention intervention (SUPPORT intervention) that was designed for and tailored to the unique experiences of veterans with SMI. This paper describes a protocol for a pilot randomized controlled trial aiming to preliminarily evaluate this peer specialist-delivered suicide prevention intervention program for veterans with SMI. The specific aims of this pilot study are as follows:

To evaluate the feasibility and acceptability of SUPPORT versus enhanced standard care. We hypothesize that SUPPORT will be feasible to deliver, as measured through attainment of recruitment goals and retention rates of ≥70%, with high satisfaction ratings.To determine the preliminary impact of SUPPORT compared to enhanced standard care on personal recovery, suicide ideation severity, and domains of veteran functioning to determine whether a larger trial is warranted. We hypothesize that SUPPORT compared to enhanced standard care will yield greater enhancement of personal recovery and reduction in suicide ideation severity (primary outcomes), as well as enhanced psychosocial functioning, quality of life, and suicide prevention strategy recall.

## Methods

### Setting

This pilot randomized controlled trial is taking place in the Veterans Affairs (VA) San Diego Healthcare System. Recruitment sites are the medical center and the community-based outpatient clinics providing behavioral health care services.

### Ethical Considerations

The SPIRIT (Standard Protocol Items: Recommendations for Interventional Trials) reporting guidelines for clinical trials were used [19]. The trial was registered on ClinicalTrials.gov (NCT05537376; see Multimedia Appendix 1). This protocol was approved by the VA San Diego Healthcare System institutional review board (H210132). The institutional review board requires regular updates on the status of the project, including the number of participants enrolled, adverse events or unanticipated problems, number of withdrawals from the project, complaints about the research, and any protocol changes. The institutional review board also audits the consent forms quarterly and ensures that appropriate HIPAA (Health Insurance Portability and Accountability Act) information is included, with full regulatory audits taking place every 3 years. Taken together, the use of these methods allows for adequate evaluation of and response to the data and safety monitoring of both potential enrollees and actual participants.

All participants will provide written informed consent, as detailed in the Recruitment, Screening, and Enrollment Procedures section. It is clear in the consent form that SUPPORT is the experimental condition that is being added to the standard care that a veteran would receive. As part of informed consent, participants are told that they may withdraw from the study at any point without penalty, VHA will cover any care if harm occurs as part of their participation, and veteran participants randomized to SUPPORT may drop out of the intervention and continue with research assessments. Data collected are stored separately from protected health information, including electronic data that are only stored on the VHA network and are password protected, whereas hard copy data remain on VHA property behind 2 locks. Data are only accessible by those approved on the institutional review board protocol. Veteran participants are compensated with up to US $260 for completing all research assessments. Peer specialist participants are not eligible for monetary compensation due to their VHA employment and the federal funding mechanism; they are delivering the intervention as part of their regular tour of duty. Due to the nature of peer services being augmentative, all veteran participants are encouraged to maintain their other ongoing behavioral health care.

### Participants

#### Peer Specialist Participants

All VA San Diego Healthcare System–employed certified peer specialists are potentially eligible to be recruited into the study. All local peer specialists will be invited to the SUPPORT training as a service to the medical center per conversations with local leadership, although they must meet inclusion criteria to deliver the SUPPORT intervention. All VHA employees are required to maintain basic competencies in suicide prevention screening and referral procedures [20]. Thus, study inclusion criteria are (1) a minimum of 2 years of experience after certification as a peer specialist and (2) provision of verbal or written consent by the peer specialist for research staff to discuss their ability to participate with their direct clinical supervisor. The peer specialist’s direct clinical supervisor must agree to allow the peer specialist time as part of their current scope of practice to (1) participate in the 8-hour SUPPORT training, (2) participate in the study’s biweekly group supervision, and (3) take on at least one SUPPORT veteran participant at a given time.

#### Veteran Participants

The inclusion criteria are purposefully broad and include veterans who report active suicide ideation in the previous month (ie, Columbia–Suicide Severity Rating Scale, C-SSRS [21], score of ≥2) or suicide behavior in the previous 3 months. Additional inclusion criteria are (1) current SMI diagnosis (ie, “a mental, behavioral, or emotional disorder resulting in serious functional impairment, which substantially interferes with or limits one or more major life activities” [22]) and (2) capability to provide informed consent (via the University of California, San Diego, Brief Assessment of Capacity to Consent [23]). Prioritized SMI diagnoses include those with psychosis or bipolar symptoms. Veterans with a diagnosis that falls under the broad VHA definition of SMI, which includes the following—major depressive disorder, schizophrenia spectrum and other psychotic disorders, bipolar disorders, obsessive-compulsive disorder, panic disorder, posttraumatic stress disorder, and borderline personality disorder [24]—are eligible. To prioritize those with psychosis and bipolar symptomology, recruitment will be expanded to the broad SMI diagnoses if no veterans meet the criteria for psychosis-related or bipolar disorders, with a guideline that 4 out of every 5 veterans recruited should experience psychosis or bipolar symptoms.

The following are the exclusion criteria: (1) inability to complete the assessment battery, (2) current intoxication requiring immediate detoxification or an outpatient plan directed specifically to residential substance use disorder (not mental health) services, and (3) imminent psychiatric hospitalization. We will include participants with an active substance use disorder if they do not require acute detoxification or residential treatment, and they can participate after acute detoxification. Participants can be engaged in other forms of treatment, including psychotherapy, as SUPPORT is meant to augment existing treatment as is standard of peer services. Veterans who participated in the previous open pilot trial will not be eligible to participate in the pilot randomized controlled trial to allow for the intervention to reach a broad range of veterans.

### Recruitment, Screening, and Enrollment Procedures

#### Peer Specialist Participants

Research staff presented to the local peer specialists during their monthly team meeting to introduce the study. Peer specialists who met eligibility criteria were invited to follow up with research staff if they were interested in participating and instructed to provide verbal or written consent for research staff to contact their direct clinical supervisor. Next, the research staff contacted the peer specialists’ direct clinical supervisors to discuss inclusion criteria. If eligibility was determined, they were consented and enrolled in the study. If they were not eligible, they were informed and still invited to participate in the SUPPORT trainings.

#### Veteran Participants

The veteran recruitment processes were designed to produce minimal impact to usual care. The primary recruitment locations for this study include VHA inpatient and outpatient behavioral health clinics, emergency services, and specialty services (eg, suicide prevention coordinators) across the VA San Diego Healthcare System. Potential veteran participants are recruited via three primary avenues: (1) veterans accessing same-day services, (2) veterans with recent documented suicide ideation or behavior, and (3) VHA clinician referrals. Veterans may also self-refer. Usual care for any veteran accessing same-day services involves a diagnostic interview with a triage provider and a psychiatric evaluation, which includes the VHA system-wide standardized Comprehensive Suicide Risk Evaluation (CSRE) and, as indicated, referrals to outpatient mental health services following evaluation. VHA clinicians are required to screen veterans yearly for suicide risk via the C-SSRS screener [21,25] and document this in the veteran’s electronic health record. The C-SSRS screener is also used by VHA clinicians as clinically indicated and is required upon transitions of care (eg, discharge from inpatient psychiatry).

Research screening is used to confirm eligibility. Research staff will be available on the same day to accept a “warm handoff” for screening as needed. For all veterans contacted for screening, a CSRE will be conducted subsequently by the on-call psychologist if their risk level has changed since their last documented CSRE. If the veteran is deemed to be at moderate or high risk, a suicide safety plan will be completed or reviewed and updated. If the veteran is eligible, they will be invited to participate in a separate informed consent meeting and then subsequently enrolled in the study. Following enrollment, veteran participants will complete a diagnostic and baseline assessment and then randomized to SUPPORT or enhanced standard care. Those randomized to the SUPPORT condition will be matched with a peer specialist participant based on the peers’ and veteran’s availability. Randomized matching and veteran preference were considered but deemed not to be feasible given the nature of the pilot design. As feasible, veteran preference for identity characteristics such as gender as well as shared lived experience will be considered in matching as is standard practice for VHA peer services. Veterans not eligible at any stage will receive standard mental health care referrals and a study-designed resource packet.

Specific to allocation of conditions, a computer-generated 50-participant randomization table for this study was created and will be maintained by the project’s biostatistician. The table includes no matching on baseline characteristics, 1 follow-up assessment as the minimum number of follow-up assessments needed to be considered as intention to treat, and completion of a minimum of 1 module of the intervention to be considered as intention to treat for those in the SUPPORT condition. After enrollment, the study coordinator emails the veteran participant’s unique identification number to the biostatistician, who then provides the study coordinator with the allocation. There is no masking due to the pilot feasibility and acceptability design. See Figure 1 for the veteran participant timeline flow.

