#### Primary and Secondary Outcomes

Primary and secondary outcomes will be tested using mixed-effects models [64,66]. This method allows for the inclusion of participants with missing data and those who dropped out without relying on data imputation. It provides an estimate of the individual variability around the population trend and the variability of the individual intercepts (baseline values) and slopes (changes across time and the correlation between them). A fully saturated treatment by visit model will be used for inference. Covariate structure will be chosen based on the Akaike information criterion. Data will be analyzed for all participants who were randomized for whom we have a baseline assessment and at least one follow-up assessment. We expect the dropout rate to be <10% after the baseline assessment (this dropout rate is considered in our power analysis estimation).

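### The protocol's intention-to-treat definition requires a completed module in the SUPPORT arm only, which is not intention to treat and contradicts the analysis set in the outcomes section

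*Protocol article*

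**What the plan says.** Two sections of the protocol article say who counts in the comparison, and a third bears on who will have data.

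- **Recruitment, Screening, and Enrollment Procedures, Veteran Participants.** The paragraph on allocation lists two conditions for intention-to-treat status. For both arms it gives "1 follow-up assessment as the minimum number of follow-up assessments needed to be considered as intention to treat". For one arm it adds "completion of a minimum of 1 module of the intervention to be considered as intention to treat for those in the SUPPORT condition". The same section puts randomisation after baseline: veterans "will complete a diagnostic and baseline assessment and then randomized to SUPPORT or enhanced standard care". It also states "There is no masking due to the pilot feasibility and acceptability design".
- **Analysis of Outcomes, Primary and Secondary Outcomes.** "Data will be analyzed for all participants who were randomized for whom we have a baseline assessment and at least one follow-up assessment". Modules are not mentioned. The mixed model is justified on the ground that "This method allows for the inclusion of participants with missing data and those who dropped out without relying on data imputation".
- **Ethical Considerations.** Consent tells veterans that "veteran participants randomized to SUPPORT may drop out of the intervention and continue with research assessments".

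**The concern.** Intention to treat means that membership of the analysis is fixed by allocation. A condition that can be met only after allocation, and only in one arm, removes that protection. Veterans who never complete a first module are unlikely to be a random subset. The article's own background points to cognitive and functional impairments that may affect uptake of prevention strategies, and starting also depends on whether a peer specialist and the veteran are both available. Similar veterans in enhanced standard care cannot be identified and would stay in. The filtered SUPPORT arm would then be compared with an unfiltered control arm on personal recovery and suicide ideation severity.

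The second problem is that the article gives two analysis sets and does not say which governs. In an unmasked trial, an ambiguity of this kind should not be left to be settled once allocations and outcomes are known. The between-arm comparison also has a purpose: the Objectives use it to judge whether a larger trial is warranted.

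**Working it through.** **Step 1. Set the two definitions side by side.** All cases are randomised veterans with a baseline.

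| Veteran | Recruitment section | Outcomes section |
|---|---|---|
| Control, at least 1 follow-up | in | in |
| Control, no follow-up | out | out |
| SUPPORT, at least 1 module, at least 1 follow-up | in | in |
| SUPPORT, at least 1 module, no follow-up | out | out |
| SUPPORT, no module, at least 1 follow-up | **out** | **in** |
| SUPPORT, no module, no follow-up | out | out |

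The definitions differ in one row, and that row exists in one arm only. Ethical Considerations shows that it can be populated, because a veteran may leave the intervention and still be assessed. A veteran who leaves after completing module 1 is not affected.

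**Step 2. Formula for the bias if the module rule is applied.** Among SUPPORT veterans with at least one follow-up, let q be the share with no module and g the amount (in SD) by which their outcomes are worse than those of starters. If starters have mean m:

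- whole arm: (1 − q)·m + q·(m − g) = m − q·g
- filtered arm: m
- bias = m − (m − q·g) = q·g, in favour of SUPPORT when g > 0 and against it when g < 0.

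**Step 3. Put numbers in.** The document gives neither q nor g, so both are assumptions. The reference effect is the 0.7 SD at the last time point in the sample size section.

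- Low: 0.10 × 0.3 = 0.03 SD; 0.03 / 0.7 = 4%.
- High: 0.20 × 1.0 = 0.20 SD; 0.20 / 0.7 = 29%.
- Wider grid, q 5-30% and g 0.25-1.0: from 0.05 × 0.25 = 0.0125 SD (2%) to 0.30 × 1.0 = 0.30 SD (43%).

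**Step 4. Effect on type I error with no true effect.** This is a two-sided 5% normal approximation. The residual SD is √(1 − 0.5²) = 0.87, reading the printed repeated-measures correlation as 0.5. There are 25 per arm before exclusion; the article describes "a computer-generated 50-participant randomization table for this study was created" but states no ratio, so 25:25 is assumed. SE = 0.87 × √(1/(25(1 − q)) + 1/25).

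| q | g (SD) | bias (SD) | SE (SD) | type I error |
|---|---|---|---|---|
| 10% | 0.5 | 0.05 | 0.25 | about 0.055 |
| 20% | 0.5 | 0.10 | 0.26 | about 0.067 |
| 20% | 1.0 | 0.20 | 0.26 | about 0.120 |
| 30% | 1.0 | 0.30 | 0.27 | about 0.20 |

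**Step 5. Why q is smaller than the raw non-start rate.** Both definitions already exclude veterans with no follow-up. Suppose 5 of 25 SUPPORT veterans (20%) complete no module and the other 20 all have a follow-up. If all 5 attend a follow-up, q = 5/25 = 20%. If only 2 do, q = 2/22 = 9%, and at g = 0.5 the bias is about 0.05 SD instead of 0.10 SD.

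**The case against.** The strongest reply is that the section fixing the analysis has no module condition. The other sentence sits under recruitment, describes the randomisation table and names no outcome model. On that reading the comparison is never filtered. This stands in part: a reader might infer that the trial's comparison is biased as planned, and the document does not support that. The bias is conditional on the recruitment-section rule being applied. The reply does not remove the contradiction or make the definition correct. If the outcomes section governs, the other sentence is wrong and should go.

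The size is also open to challenge. Both inputs and the direction are assumed, and the mid-range bias of 0.05-0.10 SD is small beside a standard error of about 0.25 SD. That is fair. A reader might likewise infer that about 3-5 of 25 SUPPORT veterans would be lost to this rule (10-20% of 25 is 2.5 to 5). That is an upper figure, because it assumes every non-starter attends a follow-up.

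Two further inferences are tempting and not supported. One is that retention and acceptability would be flattered too. Feasibility and Acceptability Data defines retention for veterans at the end of the intervention and does not tie either measure to an intention-to-treat set. The other is that requiring one follow-up conflicts with the claim that the mixed model keeps dropouts. It does not: a veteran who leaves after one follow-up is included, and the condition is the same in both arms and in both sections.

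Finally, this is a pilot whose primary goal is feasibility and acceptability, and the article admits that it may be underpowered. That lowers the stakes of the efficacy comparison. It does not excuse an incorrect definition in a comparison meant to inform a larger trial.

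**Conclusion.** The point holds as a wrong definition and an internal contradiction. The one-module condition is a post-randomisation filter on one arm under an intention-to-treat label, and it disagrees with the analysis set in the outcomes section for exactly one group: SUPPORT veterans with no module and at least one follow-up.

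If the condition were applied, the bias would be q × g. The illustrative range is 0.03-0.20 SD, or 4-29% of the 0.7 SD target, for q of 10-20% and g of 0.3-1.0 SD. It rests on three assumptions that the document cannot confirm: the share of non-starters who attend a follow-up, the size of their outcome gap, and that they do worse than starters. If they do better, the bias runs against SUPPORT. If the outcomes section governs, the bias from this source is zero.

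**What to change.** - In Recruitment, Screening, and Enrollment Procedures, delete the one-module condition from the intention-to-treat definition.
- Align that section with Primary and Secondary Outcomes, and state in both that randomised veterans are analysed in their assigned arm whatever their module completion.
- Label any analysis limited to veterans with at least one completed module as a secondary per-protocol analysis.
- Optionally, keep veterans with a baseline only in the longitudinal model, with baseline as part of the outcome vector. This is minor, because the follow-up condition applies equally to both arms.

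The cost is a change of wording, with no extra data or participants. Data collection is projected to run until May 2027, so the correction can be made before analysis.
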